#### Effectiveness of the home-based AOMI intervention

2.5.3

##### Primary outcomes

2.5.3.1

The Chinese version of the Neuropsychiatry Unit Cognitive Assessment Tool (NUCOG) will be used to assess global cognitive function (41). This brief cognitive screening tool, specifically designed for neuropsychiatric patients (42, 43), has demonstrated clinical utility among individuals with SCI. The NUCOG consists of 21 items in 5 cognitive domains—attention, visuoconstructional ability, memory, executive function, and language—assigning scores from 0 to 20 for each area, resulting in a maximum total score of 100. Higher scores indicate higher levels of cognitive function. Due to the motor skills required for standard administration, survivors with SCI who have restricted or no hand function may face challenges. For those subjects, the adapted version of the NUCOG by Craig et al. will be utilized, a modification that does not affect the validity of NUCOG (44).

*Depression*: The level of depression will be evaluated using the second version of the Beck Depression Inventory (BDI-II), which consists of 21 items that assess two factors (cognitive and affective, and somatic symptoms) (45). The total possible score of BDI-II is 0 to 63; higher scores reflect higher levels of depression. The BDI-II has exhibited adequate reliability (Cronbach’s *α* coefficient of 0.94) when applied among individuals with SCI (46).

##### Secondary outcomes

2.5.3.2

*Attention*: The Digit Span Test [Forward Span] and the oral version of the Symbol Digit Modalities Test (SDMT) will be used to assess attention. Referring to the former test, the examiner pronounces a list of digits at a rate of approximately one digit per second, and subjects are required to immediately repeat the list in the same order (47). Digit Span has high internal consistency, reliability, and construct validity (48). The SDMT involves participants verbally matching symbols with digits within a 90-s time frame (49). Higher numbers of correct responses indicate superior cognitive processing speed. The SDMT demonstrates good test–retest reliability and sensitivity to cognitive impairments across diverse populations (50).

*Executive function*: The Stroop Color Word Test and the Digit Span Tests [Backward Span] will be used. We will determine the former by subtracting the Color (congruent trials) from the Color-Word (incongruent trials) scores. It is a measure of response competition and interference with moderate-to-good reliability (51). Scoring is based on the time it takes to read (complete) incongruent trials relative to congruent trials. The backward digit span task uses the same procedure as the Digit Span forward task, except that in this case, subjects have to reproduce the sequence of digits in reverse order (52).

Multimodal MRI will be used to uncover possible mechanisms underlying the effectiveness of the AOMI intervention. The brain scanning session lasts around 40 min and includes the following sequences: T1-weighted anatomical scan for regional volume measurement, resting-state functional MRI (rs-fMRI) for assessing functional connectivity features and neural networks, task-based fMRI to indicate specific brain regions activated during AOMI tasks, and diffusion tensor imaging (DTI) to reflect the microstructural integrity of white matter tracts (53). During the rs-fMRI scan, subjects will be instructed to lie at rest with eyes open and fix on a bright cross-hair on a dark background. During the task-based fMRI, the subjects will be instructed to perform an “AOMI” fMRI task: subjects will be asked to imagine themselves performing the same exercise while watching the video representing wheelchair exercises. Videos will be presented from a dual perspective (first-person and third-person), and subjects will be asked to identify themselves and mentally simulate each situation (without moving the body). AOMI videos are alternated with resting periods in which subjects will be instructed to observe a static picture from the videos. The main acquisition parameters for each modality are listed in Supplementary Table S4. The multimodal MRI scans will be completed at the University Research Facility in Behavioral and Systems Neuroscience pre- and post-intervention on a 3-Tesla Siemens Prisma scanner, with a 32-channel head coil.

*Chronic pain*: The Chinese version of the Brief Pain Inventory (BPI-C) will be used to assess pain severity and interference (54). This questionnaire has been used in patients with SCI, with higher scores representing more violent pain (55).

*Self-efficacy for exercise*: The 9-item Chinese version of the self-efficacy for exercise (Cronbach’s *α* = 0.90) will be used to evaluate participants’ confidence level (from 0, not confident, to 10 very confident) regarding engaging in regular exercise (56). A higher score indicates greater exercise self-efficacy.

*Motor imagery ability*: The short version of the Kinesthetic and Visual Imagery Questionnaire (the KVIQ-10) will be used to evaluate the participants’ motor imagery ability (57). This questionnaire has 10 items, assessing both the visual and kinesthetic components of MI, and is particularly suitable for people with disabilities. The Chinese version of the KVIQ has been validated among stroke patients, showing good reliability and construct validity (49).

### Sample size and sampling

2.6

The central limit theorem posits that a minimal sample size of 30–40 is enough for determining the mean, standard deviations, and 95% confidence intervals (58). This pilot RCT aims to assess the feasibility, acceptability, and preliminary effectiveness of the AOMI intervention, utilizing a generally acceptable sample size for preliminary analysis to evaluate intervention feasibility and estimate the between-group effect. Specifically, each study group will have 18 individuals to identify a standardized effect size of 0.40 with 80% power and a two-sided significance level of 5% (59). Taking into account a potential attrition rate of 20%, 23 participants per group (i.e., 46 participants in total) will be recruited by using convenience sampling. For one-on-one interviews, we will use a purposeful sampling of key informants, including those who completed at least 60% of the intervention sessions and those who did not, until we reach information saturation and find no relevant new codes in the data (60).

For MRI scans, a liberal threshold of *α* = 0.05 requires 24 participants (12 per group) to achieve 80% power at the single-voxel level for typical activations (61). To control error rates in multiple comparisons, doubling the number of participants is recommended to maintain this level of power. Due to the challenges of MRI data collection, each group will consist of a minimum of 12 participants undergoing pre- and post-intervention MRI scans. Notably, this sample size aligns with the median sample size observed in highly cited clinical fMRI studies published over the last three decades (62).

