#### Quantitative data analyses

2.7.1

Quantitative data analyses will be conducted using IBM SPSS Statistics for Windows (Version 26.0. Armonk, NY: IBM Corp), with all statistical tests being two-sided and significance set at 0.05. The outcomes will be analyzed with an intention-to-treat approach (63). As for statistical description, the count data, such as gender will be presented as “frequency” and “percentage.” The continuous data that conform to the normal distribution (assessed by the W test coupled with a histogram) will be described using means ± standard deviation. As for group differences at baseline, post-intervention, and follow-up, *t-test* or Mann–Whitney *U* test will be performed for continuous variables; Pearson χ2 tests or Fisher exact test will be used for dichotomous variables. The generalized estimating equation (GEE) model, which could test the effects of group, time, and their interactions, will be used to analyze the effects of the intervention. Covariance (if any found in the baseline comparison) will be adjusted during the analysis of intervention effects. Cohen’s *d* will be used as the unit measure of effect size, and is interpreted as follows: 0.2 represents a small effect, 0.5 a moderate effect, and 0.8 a large effect. Cohen’s *d,* calculated by using the formula “difference in treatment and control group means divided by the pooled standard deviation,” is applicable for small sample sizes (64).

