This pilot RCT adopts a multidisciplinary approach, incorporating psychological, neurological, and neuropsychological assessments. The utilization of multimodal MRI enables a better understanding of the neural mechanism behind the AOMI and post-SCI neuroplastic changes. These findings will establish an empirical foundation for developing mechanism-driven interventions targeting cognitive impairment and depression in adults with SCI.

This study has several limitations that should be acknowledged. First, this pilot RCT can only show the preliminary effectiveness of the home-based AOMI intervention. Furthermore, the small sample size and potential selection bias resulting from convenience sampling may limit the generalizability of the findings. However, the results of this pilot study will provide valuable insights for designing a future full-scale RCT, which could generate much-needed level one evidence regarding the effectiveness of AOMI. Second, due to the inherent nature of the intervention, neither the interventionists nor the participants could be effectively blinded. Although we will implement weekly phone monitoring of intervention adherence and design an active control condition, potential performance bias may remain a limitation. Third, a defining characteristic of AOMI is the absence of overt physical actions during the imagery process. This inherent feature makes objective performance evaluation challenging, as AOMI relies on mental movement representation. We will employ qualitative methods (i.e., training diaries and post-intervention interviews) to assess whether participants really engaged in AOMI and whether they truly imagined the intended content. However, integrating objective methods such as neuroimaging techniques would better evaluate intervention fidelity. Due to resource constraints, we will consider this monitoring method in future research.

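### The central limit theorem does not make 30–40 participants enough to determine means, SDs and intervals, and the planned size estimates the between-group effect only to about ±0.68 SD unadjusted, against a target of 0.40

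*Protocol article*

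**What the plan says.** Section 2.6 (Sample size and sampling) of the protocol article gives two supports for the sample size.

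- A general one: "The central limit theorem posits that a minimal sample size of 30–40 is enough for determining the mean, standard deviations, and 95% confidence intervals". The section then calls the size acceptable for a preliminary analysis whose purpose is "to evaluate intervention feasibility and estimate the between-group effect".
- A specific one: "each study group will have 18 individuals" "to identify a standardized effect size of 0.40", with 80% power and a two-sided 5% level. This is raised to 23 per group, 46 in total, for 20% attrition.

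No precision target or expected interval width is given. Section 2.7.1 (Quantitative data analyses) says that Cohen's d, the mean difference over the pooled SD, "will be used as the unit measure of effect size". The Discussion calls the effectiveness findings preliminary, lists the small sample as a limit on generalizability, and says that "the results of this pilot study will provide valuable insights for designing a future full-scale RCT".

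**The concern.** The central limit theorem concerns the shape of the sampling distribution of a mean as the sample grows. It names no sample size. It does not bear on how closely an SD is estimated, and approximate normality does not make an interval narrow. The sentence therefore attributes to a theorem an adequacy that the theorem does not provide, and it does so where readers look for the justification of the sample size.

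The quantities of interest here are also not a single mean. They are a difference between two arms and the SDs behind it, and these rest on 18 completers per arm. A reader who accepts the sentence will take the pilot's effect size and SDs as better determined than they can be.

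**Working it through.** **Inputs.** From section 2.6: 18 completers per group, 23 recruited per group, standardized effect 0.40, 80% power, two-sided 5%, 20% attrition. From section 2.7.1: Cohen's d as the effect-size unit. The correlation between visits is not given, so any value used below is an assumption.

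**1. The plan's own figures.**
- Attrition: 18 / 0.80 = 22.5, rounded up to 23. This reproduces.
- Sample size for d = 0.40, two arms, normal approximation: n = 2 × (1.960 + 0.842)² / 0.40² = 98.1, so 99 per group. The t-test solution is 99.1, so 100. The stated 18 does not reproduce.
- Power for d = 0.40 at 18 per group: 22% (normal) or 21% (t-test). At 23 per group: 27% or 26%.
- Effect detectable with 80% power: 0.93 (normal) to 0.96 (t-test) at 18 per group; 0.83 to 0.84 at 23.
- Baseline-adjusted analysis: reaching 18 per group needs 1 − ρ² = 18/99, so ρ ≈ 0.90.

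**2. Precision of the between-group difference, in SD units, one visit, unadjusted.** Half-width = t(0.975, 2n − 2) × √(2/n).
- n = 18: 2.032 × 0.333 = 0.68.
- n = 23: 2.015 × 0.295 = 0.59.

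An observed d of exactly 0.40 has an approximate interval of 0.40 ± 1.96 × √(2/n + 0.40²/(4n)): −0.26 to 1.06 at n = 18, and −0.18 to 0.98 at n = 23. Both include zero.

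**3. The same with baseline adjustment.** Multiply the half-width by √(1 − ρ²).

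| Assumed ρ | n = 18 | n = 23 |
|---|---|---|
| 0.5 | 0.59 | 0.51 |
| 0.7 | 0.48 | 0.42 |
| 0.8 | 0.41 | 0.36 |

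Only one cell, 23 per arm with ρ = 0.8, falls below 0.40, and it requires no attrition.

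**4. Precision of the SD.** The 95% limits, as multiples of the estimate, are √(df/χ²) at the 97.5% and 2.5% points.
- One arm of 18 (df 17): 0.75 to 1.50.
- Pooled over 36 (df 34): 0.81 to 1.31.
- A single sample of 30: 0.80 to 1.34. A single sample of 40: 0.82 to 1.28.

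Even in a single sample of the size that the sentence names, the SD is uncertain by roughly a fifth downwards and a third upwards.

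**The case against.** **The theorem sentence is background.** The numbers 18, 23 and 46 follow from the power sentence, and deleting the theorem sentence would leave them unchanged. This stands. A reader might infer that the sample size rests on the theorem alone, and the section does not support that. But the power sentence does not rescue the rationale, since it fails on its own terms for Cohen's d.

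**The 0.40 may be a different effect size.** Read as Cohen's f (d = 0.80) in a between-groups repeated-measures ANOVA with three visits and a correlation of 0.5, the total is 36. On that reading the half-width for the mean of three visits is 0.677 × √(2/3) = 0.55, below 0.80. The article states neither f nor a correlation, and it names Cohen's d as its unit. Even so, the sentence about the theorem would remain wrong.

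**The planned analysis is a repeated-measures GEE.** The ±0.68 is for an unadjusted comparison at one visit and is not a fixed property of the trial. This stands, which is why the range in step 3 belongs beside it.

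**Any 80%-powered trial has an interval wider than its target.** At exactly 80% power the full width is about 1.4 times the target effect, so full width is a weak yardstick. The half-width comparison is the one that counts.

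**It is a pilot, and it says so.** Preliminary aims are acknowledged, and a pilot may be small. But the section itself gives estimation of the between-group effect as a purpose, and the stated limitation concerns generalizability, not precision.

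**Conclusion.** The sentence is wrong as a statement about the central limit theorem, and the adequacy it implies does not hold for this design. The unadjusted half-width is 0.68 SD at 18 per arm and 0.59 at 23, against a target of 0.40. With an assumed baseline correlation of 0.5 to 0.8 it is 0.59 to 0.41, or 0.51 to 0.36 with all 23 retained. These figures assume equal arms, a common SD and a comparison at one visit.

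The larger numerical error is the adjoining power claim: about 22% power rather than 80% if 0.40 is Cohen's d, with about 0.95 SD detectable at 80% power.

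Some stronger readings go beyond the documents:

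- A reader might infer that the pilot's SD and effect size will set the next trial's sample size. The Discussion promises only insights for its design. If the pooled SD from 36 completers were used that way, a sample size proportional to its square could be off by a factor of 0.65 to 1.72 (0.81² to 1.31², from unrounded limits). That is conditional on a use that the article does not state.
- A reader might infer that the range of 30–40 is meant as a total. The section does not say. The 36 completers fit the range; the 46 recruited and the 18 per arm do not.
- Nothing here shows that 46 is too few for a pilot. The fault is in the justification given for it.

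**What to change.** In section 2.6:

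1. Delete the sentence on the central limit theorem.
2. State the expected precision in its place, for example: *With 36 completers (18 per group), the unadjusted 95% confidence interval for the between-group difference at one visit is about ±0.68 SD; it will be narrower with adjustment for baseline.*
3. Correct or remove the claim of 80% power for an effect of 0.40 at 18 per group. It cannot stand beside the precision statement if 0.40 is Cohen's d. If another effect-size measure or a repeated-measures calculation was meant, name it and give its assumed correlation.

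In section 2.7.1, say that Cohen's d will be reported with its 95% confidence interval.

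The cost is wording only. Enrolment and assessments do not change. The price is a less favourable, but accurate, statement of what the pilot can estimate.

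### The stated 80% power for a standardized effect of 0.40 with 18 per group is wrong on the protocol's own Cohen's d scale: an unadjusted single-visit comparison has about 21%

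*Protocol article*

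**What the plan says.** Section 2.6 (Sample size and sampling) of the protocol article states that "each study group will have 18 individuals to identify a standardized effect size of 0.40 with 80% power and a two-sided significance level of" 5%. It then allows for 20% attrition, so that "23 participants per group (i.e., 46 participants in total) will be recruited". The stated purpose of the sample is "to evaluate intervention feasibility and estimate the between-group effect". The section names no test, number of measurements or within-person correlation for this calculation.

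Section 2.7.1 (Quantitative data analyses) makes Cohen's d the effect-size unit, defined as "difference in treatment and control group means divided by the pooled standard deviation", with 0.2, 0.5 and 0.8 as small, moderate and large. It plans a t-test or Mann–Whitney test between groups at each time point and a GEE with group, time and their interaction for the intervention effect, "with all statistical tests being two-sided and significance set at 0.05". No other effect-size scale appears in the article.

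**The concern.** A reader who meets a standardized effect of 0.40 in a two-arm trial, in an article whose only defined effect measure is the mean difference over the pooled SD, will take it as d = 0.40, between small and moderate on the article's own scale. Eighteen per group is far too few for 80% power at that effect.

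Two things are at stake. First, a non-significant result could be read against a claimed 80% power and taken to speak against d = 0.40, when the trial would more often than not miss an effect of that size. Second, section 3 (Discussion) says the pilot will inform a full-scale trial. If 0.40 was really on another scale, that trial could inherit a target effect that is wrong by a factor of two.

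**Working it through.** **Inputs.** From section 2.6: 18 evaluable per group, 23 recruited per group, standardized effect 0.40, power 80%, two-sided 5%, attrition 20%. From section 2.7.1: effect scale Cohen's d. From section 2.1: three measurements (before, after, 1-month follow-up). The article gives no within-person correlation, so values of 0.5 to 0.8 are assumed below.

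**Attrition step.** 18 / (1 − 0.20) = 22.5, rounded up to 23. This reproduces.

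**Power step, unadjusted comparison at one visit.** The noncentrality is d × √(n/2) on 2n − 2 degrees of freedom.

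- n = 18: 0.40 × √9 = 1.20, critical t (34 df) 2.03, power 21.5% (22.4% by normal approximation).
- n = 23: 0.40 × √11.5 = 1.36, critical t (44 df) 2.02, power 26.4%.
- n for 80% power: 100 per group (99 by normal approximation).
- Effect detectable with 80% power: d = 0.96 at 18 per group, 0.84 at 23.

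The stated 80% does not reproduce. A one-sided test would not rescue it either: power at 18 per group is 32%.

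**Using baseline and repeated visits.** With a common correlation ρ between visits, baseline adjustment replaces d by d / √(1 − ρ²). Adjusting the mean of the two post-baseline visits for baseline replaces it by d / √((1 + ρ)/2 − ρ²). Power for d = 0.40 at 18 per group:

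| Assumed ρ | Baseline-adjusted, one visit | Baseline-adjusted, mean of two visits |
|---|---|---|
| 0.5 | 27% | 38% |
| 0.7 | 37% | 49% |
| 0.8 | 49% | 63% |

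Eighty percent is reached only at ρ of about 0.91 (one visit) or 0.87 (two visits). If all 23 per group were evaluable, the two-visit figures would be 47%, 60% and 74%. The baseline-adjusted detectable effect at 18 per group is 0.96 × √(1 − 0.25) = 0.83 at ρ = 0.5 and 0.96 × √(1 − 0.49) = 0.69 at ρ = 0.7.

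**Where 18 could come from.** Two undeclared repeated-measures ANOVA set-ups give a total of N = 36:

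- *Between-groups test*, f = 0.40, m = 3 measurements, ρ = 0.5. The noncentrality is f²Nm / (1 + (m − 1)ρ) = 0.16 × 36 × 3 / 2 = 8.64 on 1 and 34 df, power 81.5%. For two equal groups d = 2f, so this is d = 0.80. The tested quantity is the group difference averaged over all visits, baseline included. With f = 0.20 (d = 0.40) the same design has about 30% power.
- *Group-by-time interaction*, f = 0.20, m = 3, ρ = 0.58. The noncentrality is f²Nm / (1 − ρ) = 0.04 × 36 × 3 / 0.42 = 10.3 on 2 and 68 df, power 80.9% (78.3% at N = 34). If the groups are equal at baseline and differ by δ SD at both later visits, the interaction f² equals δ²/18, so f = 0.20 means δ = √(0.04 × 18) = 0.85.

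Neither corresponds to a post-baseline difference of d = 0.40.

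**Precision.** For an observed d = 0.40 with 18 per group, the standard error is about √(2/18 + 0.40²/(4 × 18)) = 0.34, giving a 95% CI of about −0.26 to 1.06.

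**The case against.** The power sentence does not itself say Cohen's d or t-test. The d definition sits in the analysis section and concerns reporting, and the source cited for the calculation was not available. Since 18 per group can be recovered from a three-measurement repeated-measures calculation, the arithmetic may have been sound and only its labels lost. This stands as far as it goes: the documents do not show how 18 was derived. It does not make the sentence right as written, because 0.40 is then on a scale the reader is never told about.

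It is also fair that 21% is at the low end. The intervention effect is to be analysed by GEE, which can draw on baseline and both later visits, and the table above shows the gain. A reader might infer that the trial as a whole has 21% power and would miss d = 0.40 four times in five. That holds only for the unadjusted single-visit comparison.

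A reader might likewise infer that the trial must have been sized on a visit-averaged group effect with f = 0.40. The documents do not support that, because the interaction set-up gives the same N.

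Finally, this is a pilot. Section 2.6 first justifies its size by estimation of means, SDs and confidence intervals, and section 3 concedes a small sample and only preliminary evidence of effectiveness. That limits the harm. It leaves the 80% claim in place, however, and section 3 ties the small sample to generalizability and not to power.

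**Conclusion.** The sentence is wrong as written. On the d scale, 18 per group give about 21% power for 0.40 in an unadjusted single-visit comparison (26% at 23), against the claimed 80%. The required number is understated more than fivefold (100 against 18 per group). Baseline and repeated-visit information narrows the gap but does not close it for assumed correlations up to 0.8, where the most favourable figure at 18 per group is 63%.

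The conclusion rests on reading 0.40 as Cohen's d, the only scale defined. If another measure was meant, the fault is an undeclared metric, test and correlation, and the detectable effect on the d scale is still about twice what the sentence suggests in the set-ups that reproduce 18. The point should be fixed. It does not call the trial's size, conduct or feasibility aims into question.

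**What to change.** Keep 46 participants and change the power sentence in section 2.6 in one of three ways:

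1. Restate it on the d scale: 18 completers per group give 80% power for d of about 0.96 unadjusted, or about 0.7–0.8 adjusted for baseline at an assumed correlation of 0.7–0.5; unadjusted power for d = 0.40 is about 21%.
2. If another effect measure was intended, name it together with the test, number of measurements and assumed correlation, and give the equivalent d (for f = 0.40 in the between-groups test, d = 0.80).
3. Drop the power claim and justify the number by precision, giving the expected 95% CI width for the effect (about −0.26 to 1.06 around an observed d of 0.40 at 18 per group).

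The cost is a wording change. The stated capability becomes less favourable, and no participants, visits or analyses are added.
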